## Abstract

**Background:**

In the 10 most populated countries in the world, Parkinson's disease (PD) affects more than 5 million individuals. Despite optimal treatment options already developed for the disease, concomitant involvement of other areas of health care plays an important role in complementing the treatment. From this perspective, dancing can be viewed as a non-drug alternative that can reduce falls by improving some motor skills, such as mobility, balance, gait, and posture, and can also improve the overall quality of life. Brazilian samba promotes improvement in motor and non-motor symptoms in individuals with PD, providing a new treatment option for this population.

**Objective:**

The main objective of this quasi-experimental study is to provide a 12-week samba protocol (2x/week) for individuals with PD and to compare its effects with the group without intervention. The hypothesis is that the Brazilian samba protocol will promote improvement in primary (motor) and secondary (non-motor) outcomes in individuals with PD.

**Methods:**

The sample will be selected at random from individuals diagnosed with PD in the city of Florianopolis (SC, Brazil). Sample size calculation was performed with the G*Power 3.1.9.2 software, with 0.447 effect size, at 5% significance level, power of 0.9, and test and sample loss of 20%. This yielded 60 individuals divided between the intervention and control groups. The questionnaires will be filled out before and after the dance intervention. The data collection for the control group will be held simultaneously to the intervention group. The classes will last for 1 hour, twice a week in the evening for 12 weeks, and all classes will be divided into warm-up, main part, and relaxation. Two-way analysis of variance with repeated measures and Sidak post-hoc comparison test will be used for a comparative analysis of the final results of the control group with the experimental group and of the within-group changes between pre- and postintervention period.

**Results:**

We expect to complete follow-up in September 2017.

**Conclusions:**

The major inspiration for this study was to encourage the creation of new rehabilitation programs that do not emphasize doctor involvement. This is a unique protocol for PD and we believe it can be an important tool to alleviate the motor and non-motor symptoms of individuals with PD. Dance is a simple activity depending on little equipment and few financial resources, facilitating its implementation and improving the cost-benefit relationship. In addition, activities that have a cultural aspect for the population in question, and which are pleasant, enable the participants to commit long term. This can enhance patient’s compliance with the therapy, which is often a problem for many rehabilitation programs.

## Introduction

In the 10 most populated countries in the world, Parkinson’s disease (PD) affects more than 5 million individuals and the projection is that by 2030 more than 9.3 million people will have been diagnosed [1]. Given its epidemiological importance, the disease can be considered a public health problem, manifestations of which encompass social, family, economic, and even legal problems [2], and involve high costs to the health system. Individuals with chronic diseases, such as PD, deal with physical discomforts on a daily basis arising from deficits and motor symptoms [3-6] and as autonomic, sensory, and behavioral disorders from non-motor symptoms. These can result in a severe reduction of independence [7] and quality of life in this population [8].

From this perspective, dancing can be viewed as a non-drug alternative for both symptomatologies: (1) improving some motor skills (eg, mobility, balance, gait, posture, fall reduction), and (2) improving some non-motor symptoms (eg, fatigue and depression). The benefit is an overall improvement in quality of life [9-11]. For this population, dance is perhaps the most “complete” of all interventions, mainly because the stimulation of different cerebral areas is so important for patients with PD.

Recently, Sharp et al [12] conducted a systematic review, which sought to analyze the effectiveness of dance as an intervention for PD. They found improvement in motor scores on Unified Parkinson’s Disease Rating Scale (UPDRS), balance, and gait speed in subjects who underwent dance therapy compared to the group that did not receive any intervention. Similarly, there was an improvement in quality of life when dance intervention was compared to exercise interventions [12]. In another systematic review, dance demonstrated maintenance of muscle strength and improvements in support and balance, aerobic power, full range of body movements, resulting in positive lifestyle changes in individuals with PD [13].

Among the surveys already performed with dance and patients with PD, tango is the most commonly applied ballroom dance form in studies involving PD [12]. According to Earhart [14], the practice of this particular rhythm could facilitate the activation of brain areas that normally are less active in PD. Tango movements, following a well-defined and precise rhythm, were associated with increased activation of neural areas not normally active in patients with PD [15] and with stimulation of cortical activation by increasing motor skills [16]. These results indicate that the characteristics of this rhythm may increase the demand for conscious awareness of movement in patients with PD, thus facilitating mobility [14].

Widespread in Latin America, especially in Brazil, the samba is a dance that evolved similar to tango. It was influenced by African rhythms and became popular in Europe at the same time, which explains the similarity in the execution of steps in the two rhythms [17]. Samba has a two-four time rhythm and has similar passages and diversity of execution as tango. Movement can be performed with higher or lower speed without necessarily being out of the musical time [18]. Samba marking characteristics and basic step, with stops in the movements and shifts forward and back, are similar to tango markings [19].

In addition, samba has many lively rhythms and makes use of percussion instruments, stimulating its dancers, facilitating awareness, and marking the rhythm. There are numerous styles of samba, like the slower bossa nova, or the faster gafieiras sambas [20]. This rhythm has already been used in the area of rehabilitation, with patients recovering from heart disease. It was shown that participants adapted well to the samba protocol, and it was feasible as possible exercise during cardiac rehabilitation [18].

Although the tango world is widespread, use of other dance styles could lead to more accessible and attractive interventions, when adapted to culture of the population. Furthermore, it may facilitate diversity of music [21] and application protocols. However, there is still a lack of evidence of the effectiveness of rhythms other than tango in PD. Thus, the main objective of this non-randomized study is to provide a 12-week samba protocol (2x/week) for individuals with PD and to compare its effects with the group without intervention. We hypothesize that the Brazilian samba protocol will promote improvement in primary (motor) and secondary (non-motor) outcomes in individuals with PD, providing a new treatment option for this population.

## Methods

### Study Type

This clinical non-randomized study comprises 12 weeks of intervention and monitoring of a control group (Figure 1).

### Participants

The sample will be selected at random from individuals diagnosed with PD in the city of Florianopolis (SC, Brazil). They will be recruited from a telephone list of individuals who take part in the Parkinson Association Santa Catarina. Half of those (n=30, intervention group) will be take part in activities in the Rhythm and Movement Extension Program at the Health Sciences and Sports Centre at the State University of Santa Catarina in the Santa Catarina Rehabilitation Center (CCR).

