### Data Collection

#### Experimental Group

The classes will be held at the CCR while participants are taking their medication. They will be invited to participate in the study voluntarily and to take part in the dance classes. The potential participants will be provided with an explanation of the study procedures (assessment prior to data collection, dance classes, and assessment after data collection) and the importance of attending the classes for health benefits. After the participants sign the informed consent forms, we will start collecting data. The questionnaires will be filled out before the dance intervention in a quiet place to facilitate subjects’ understanding of the questions, during a 2-week period preceding the application of the protocol. After the initial assessment, the dance classes will start twice a week and last 1 hour each time, according to the study protocol. At the end of the 12-week course, a second assessment will be held, in the same manner as the first one.

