#### Control Group

The data collection for the control group will be held simultaneously to the intervention group of the period. The researcher will schedule a visit to the patient’s home or other preferred place, where they will clarify the goals of the study, emphasize the importance of keeping to normal daily activities, and request that the patient avoids starting a physical activity during these 12 weeks. The subjects in the control group will also be advised that not performing physical activity for 12 weeks is against the guidance for prevention of disease and maintenance of health, and therefore, it is only a guideline.

The participants in the control group will be invited to monthly lectures that address the maintenance of health, prevention of falls, and psychological care. They will be asked, in person, about their general health and performance of daily activities. During the interview after the 12 weeks of data collection, any subjects who state that they have started a regular physical activity of any type will be excluded from the control group. At the end of the study, all participants (control and intervention) will receive a booklet stating, in a clear and objective way, the main results for both the group and individually (including the activities started during the period and the option to be excluded from the databank). Since the dance classes will continue after the end of the study, all participants will be invited to take part in them.

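### Random selection is claimed for consenting members of one association's list, no rule assigns the groups, and the covariate-free ANOVA cannot separate samba from other causes of differential change

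*Protocol article*

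**What the plan says.** **Sampling.** The Participants section (and the Abstract's Methods) states: "The sample will be selected at random from individuals diagnosed with PD in the city of Florianopolis (SC, Brazil". The next sentence of Participants names the source: "They will be recruited from a telephone list of individuals who take part in the Parkinson Association Santa Catarina".

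**Assignment.** Study Type says "This clinical non-randomized study comprises 12 weeks of intervention and monitoring of a control group". The Abstract's Objective calls the study quasi-experimental, and the Introduction calls it non-randomised. On who dances, Participants says only "Half of those (n=30, intervention group) will be take part in activities in the Rhythm and Movement Extension Program"; how that half is chosen is not stated in the text. The caption of Figure 1 refers to participant selection, but the figure is not shown.

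**Entry to each group.** Of the dancers, the Experimental Group section says "They will be invited to participate in the study voluntarily and to take part in the dance classes". Of the controls, the Control Group section says "The researcher will schedule a visit to the patient’s home or other preferred place, where they will clarify the goals of the study".

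**Analysis.** Statistical Analysis and Sample Size names a two-way repeated-measures ANOVA with Sidak post-hoc tests, comparing the two groups and the pre-post changes within each. The Abstract describes the between-group part as a comparison of final results. No covariate, matching or weighting is named. The one stated guard against confounding is an eligibility restriction on prior systematic physical activity (text after Figure 1).

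**Hypothesis.** It is causal: the samba protocol is expected to bring about improvement in motor and non-motor outcomes.

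**The concern.** Two separate issues meet here.

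The first is who the results apply to. Members of one association who can be reached by telephone and who consent are not a random sample of the city's people with PD. The sampling sentence therefore promises more generalisability than the recruitment can deliver.

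The second is what a group difference means. Without random allocation, and with no assignment rule in the text, dancers and controls may differ in disease stage, age, mobility or motivation. Those factors can affect how a patient's scores move over 12 weeks as well as where they start. The stated analysis contains only group and time, so a difference in change arising from such factors looks the same as an effect of samba. If the reading is taken from post-test scores or from the group main effect, a difference present before the first class is enough to produce a significant result.

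**Working it through.** The article gives no figure for selection bias, so there is none to reproduce. The check asks what each term of the stated ANOVA does when samba has no effect.

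**Inputs.** From Statistical Analysis and Sample Size: 25 evaluable per group (n = 25), alpha 0.05, two groups. From Data Collection: two assessments, before and after. Assumed, because the document gives no value: the size of the group difference, and the pre-post correlation rho. Scores are scaled to SD 1 at each assessment. Tests are two-sided with 48 degrees of freedom and critical t = 2.011.

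**1. Group-by-time term, differential change.** With two assessments this test equals a two-sample t test on change scores. If the groups differ by b SDs of change for reasons other than samba, the noncentrality is b × √(n/2) = b × √12.5 = 3.536b.

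| b (SD of change) | Noncentrality | Chance of p < 0.05 |
|---|---|---|
| 0 | 0 | 5% |
| 0.2 | 0.707 | 10.7% |
| 0.3 | 1.061 | 18.0% |
| 0.5 | 1.768 | 41.0% |

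The unit matters. The SD of change is √(2(1 − rho)) score SDs, which is 1 at rho 0.5 and 0.63 at rho 0.8. A given difference on the score scale is therefore larger in SDs of change when rho is high.

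**2. Stable offset only.** Let one group score 0.5 SD better at both assessments, with no difference in change.

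- Group-by-time term: the offset cancels in post minus pre, so b = 0. Simulation of 4,000 trials per setting gave 5.0% at both rho 0.5 and rho 0.8.
- Comparison of final scores: the difference is 0.5 SD, noncentrality 1.768, rejection about 41%.
- Group main effect: the mean of the two scores has SD √((1 + rho)/2). At rho 0.5 this is 0.866, so the standardised difference is 0.5/0.866 = 0.577, with rejection about 52%. At rho 0.8 it is 0.949, giving 0.5/0.949 = 0.527, with rejection about 44–45%.

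**3. Would regression on the baseline score cure it?** Under the same stable 0.5 SD offset, regressing the 12-week score on group and baseline leaves a bias of 0.5(1 − rho), against a residual SD of √(1 − rho²).

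| rho | Bias | Residual SD | Ratio | False positives |
|---|---|---|---|---|
| 0.5 | 0.25 | 0.866 | 0.289 | 16–17% |
| 0.7 | 0.15 | 0.714 | 0.210 | about 11% |
| 0.8 | 0.10 | 0.600 | 0.167 | about 9% |

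In non-random groups the change-score model and the baseline-adjusted model answer under different assumptions, and neither is safe in every case.

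**The case against.** **The design is disclosed.** The article openly calls itself quasi-experimental and non-randomised. A reader might infer that the sampling sentence claims random allocation. It does not: it concerns sampling, and random sampling can coexist with non-random assignment. One could even draw names at random from a telephone list. This stands. What remains is a mismatch of sampling frame, the city's patients against consenting members of one association.

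**Self-selection into the dance group is not stated.** A reader might infer from the voluntary invitation and the home visits that dancers are those who accepted classes and controls those who declined or could not travel. The text does not say so. The invitation sits beside the informed-consent text, controls may choose a place other than home, and the missing figure may show the rule. This also stands. The concern needs only that allocation is non-random and that its rule is absent from the text.

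**The ANOVA does use the baseline.** A reader might infer that the planned model corrects for no baseline difference at all. That is wrong for the group-by-time term, as step 2 shows. It is right for the comparison of final results and for the group main effect, and the article does not say which term carries the inference.

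**Eligibility narrows the groups.** Both groups must meet the same criteria on medication, physiotherapy attendance, prior activity and cognition. This reduces confounding but does not balance stage, age or motivation.

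**Covariates may appear in a fuller plan.** Possibly. But the article fixes the model and a reading of final results, and that choice can be judged as written.

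**Conclusion.** The point holds in a bounded form. The sampling claim conflicts with the recruitment described beside it, the text gives no assignment rule, and the stated analysis cannot separate a samba effect from differential change with other causes. That such a difference exists, or will be read as a samba effect, is a risk and not a certainty.

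The 11%, 18% and 41% rates apply only to the group-by-time test, with 25 per group, no samba effect and assumed differences of 0.2, 0.3 and 0.5 SD of 12-week change. The roughly 41% rejection for final scores, and 44–52% for the group main effect, rest on an assumed stable offset of 0.5 SD. No figure in the article supports any particular value.

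It would go too far to say that the study cannot inform its question, or that covariates would solve the problem. Motivation is not among the listed measures, so confounding through it would remain after adjustment. The correction should be made because it is cheap and changes what may be concluded.

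**What to change.** 1. Replace the random-selection wording in the Abstract and in Participants with the actual method: consenting members recruited from the association's telephone list. State how participants are assigned to classes or control.
2. Name the group difference in 12-week change (the group-by-time term) as the basis for inference. Do not rest conclusions on the post-test comparison or the group main effect.
3. Add Hoehn and Yahr stage, age and weekly physiotherapy frequency as baseline covariates in the model for change. Stage is listed in Table 1, and age and physiotherapy attendance are eligibility items.
4. Report alongside it, as a sensitivity analysis, a model of the 12-week score adjusted for the baseline score. Say that the two rest on different assumptions when groups are not randomised, and discuss any disagreement.
5. Limit the conclusion to an association in a non-randomised volunteer sample.

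**Cost.** Wording, a few lines of syntax, about three degrees of freedom out of 48, and a more cautious conclusion.

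Random allocation to classes now or after 12 weeks would deal with confounding at its source, and the article already invites all participants to later classes. It replaces the declared design, however, and is an option only if enrolment has not begun. The Abstract expects follow-up to be complete in September 2017.

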**Figure 1 figure1:**
[figure not shown]
Flowchart showing the process of participant selection and steps in the study protocol.

Inclusion criteria consist of individuals of both sexes; aged ≥50 years; with a clinical diagnosis of PD, according to the criteria of the London Brain Bank [22]; on stable doses of medication; who attend one or two times weekly, a physiotherapy section and who have not participated in any dance classes for at least 3 months. Exclusion criteria consist of people who are taking part in combined practice of any physical activity program and/or exercise; fail to complete all stages of the study (intervention); are decompensated clinically; do not meet the cut-off points on the Mini-Mental State Examination, in accordance with the criteria established by Bertolucci et al [23] for the Brazilian population (13=illiterate, 18=medium level of education, 26=high school); and with physical disability affecting daily or social life activities, due to a condition other than PD.

In order to avoid confusion bias before the intervention, participants will be excluded from either of the groups, if they have participated in systematic physical activity, for at least 3 months prior to the start of the study.

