## Discussion

### Principal Findings

The major inspiration for this study was to encourage the creation of new rehabilitation programs that do not emphasize doctor involvement. A further goal was to provide an environment where patients, caregivers, and teachers can interact in a friendly and relaxed manner, while stimulating and encouraging social relations, important for maintaining of the well-being of patients [21].

Dance, already used as a rehabilitation tool with other diseases [33,34], has properties that address important aspects of PD [12,13]: music stimulates affective memory and the rhythm engages different neural regions [35]. Dance replaces treatments or exercises that sometimes discourage patients. In addition, because it embraces natural movements to the human being [36], dance stimulates control and motor actions, which are of great value to individuals with PD [10-13].

The positive results already found in similar studies lead us to believe in the potential of this intervention for these individuals. The protocol’s main characteristics are based on four pillars: gradual progression, stimulation of adaptability, constant revision, and provision of a lively environment during the activities. The first two pillars mainly involve motor symptoms such as gait control and balance, while the last two pillars stimulate non-motor symptoms such as cognitive stimulation and memory, providing an enjoyable activity leading to a reduction in fatigue and depressive symptoms, in addition to stimulating social interaction.

The gradual progression of difficulty of the exercises will facilitate learning and give students the motivation to learn new steps. Introduction of new steps every 2 weeks (except when the turns are taught) is extremely important in PD because the motor skills essential to daily activities often require adaptability to changing environments and the ability to deal with unpredictable fluctuations in the disease. Therefore, expanding the motor skills repertoire must be constant [9].

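### Entry requires weekly or twice-weekly physiotherapy, but the prior-activity exclusion does not exempt it, and its frequency is left out of a non-randomized comparison on motor outcomes

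*Protocol article*

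**What the plan says.** Three rules stand close together in the Participants section under Methods, in the text after Figure 1.

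- Inclusion: patients "who attend one or two times weekly, a physiotherapy section". A further condition bars recent dance classes.
- First exclusion: "people who are taking part in combined practice of any physical activity program and/or exercise".
- Second exclusion, in a separate paragraph meant to prevent confounding. It applies to both groups and removes people "if they have participated in systematic physical activity, for at least 3 months prior to the start of the study".

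The Control Group section adds rules for follow-up. The researcher is to "emphasize the importance of keeping to normal daily activities, and request that the patient avoids starting a physical activity during these 12 weeks". At the interview after the 12 weeks, "any subjects who state that they have started a regular physical activity of any type will be excluded from the control group". The Experimental Group section has no matching request or exclusion.

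The Study Type section calls the study non-randomized. The Outcome Measures section names motor function and balance as primary, and the sample size is built on UPDRS III. The analysis is a two-way repeated-measures ANOVA with Sidak comparisons. No covariate is named.

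**The concern.** One rule makes physiotherapy compulsory. Another removes people for systematic physical activity without saying on which side of the line physiotherapy falls. A rule whose stated purpose is to prevent confounding should not leave open whether a therapy that every participant receives is covered by it.

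It also matters for the comparison. Physiotherapy may act on the same motor outcomes as the dance, and it may be taken once or twice a week. Without randomization there is no reason to expect the two frequencies to be equally represented in the two groups. If they are not, the difference shows up as a samba effect or masks one, and the stated model cannot separate the two.

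**Working it through.** No figure in the article rests on this point, so the check is mainly a comparison of texts.

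**Inclusion against the first exclusion.** The exclusion refers to combined practice but does not say combined with what. After an inclusion rule that names physiotherapy, it can be read as exercise on top of physiotherapy. On that reading the two rules agree. The wording is unclear, but the pair is not a contradiction.

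**Inclusion against the second exclusion.** This sentence has neither the word combined nor an exception, and it applies to both groups. There are two cases.

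1. Physiotherapy does not count as systematic physical activity: the rules are compatible, but the article never says so.
2. Physiotherapy does count: a patient who has attended weekly for three months or more meets the inclusion rule and fails the exclusion. Only patients who began physiotherapy more recently would satisfy both rules.

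The Control Group section leans towards the first case. It warns controls that going 12 weeks without physical activity runs against health guidance, although each of them must be attending physiotherapy. That is an inference about intent and not a stated exemption.

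**Follow-up.** The week-12 rule removes controls who have started regular activity. Whether a control who goes from one physiotherapy session a week to two has started something is not defined. No equivalent exclusion is stated for the dance group.

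**Permitted amount of physiotherapy over the study.**

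- Once weekly: 1 × 12 weeks = 12 sessions.
- Twice weekly: 2 × 12 weeks = 24 sessions.
- Samba: 2 × 12 weeks = 24 classes.

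Two eligible participants can therefore differ by 24 − 12 = 12 sessions, a twofold range. The upper end equals the number of dance classes.

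**Illustration of bias.** The article gives neither the effect of a second weekly session nor the mix in each group, so both are assumed here. With bias = (effect of a second weekly session, in SD) × (difference between groups in the share attending twice):

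- Low: 0.1 SD × 0.20 = 0.02 SD.
- High: 0.4 SD × 0.50 = 0.20 SD.

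**Cost of adjustment.** With the 25 per group that the article expects to analyse, the between-subject error degrees of freedom are 50 − 2 = 48. One binary covariate leaves 47. No sample-size or power figure in the article changes.

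**The case against.** The strongest reply is that a specific rule naming physiotherapy governs a general rule that does not mention it, so a sensible recruiter would treat physiotherapy as exempt. The article also never describes the content of the physiotherapy, so calling it systematic physical activity is a premise brought from outside. Both remarks are fair. They show how the conflict would probably be resolved in practice, but the sentence still contains no exemption.

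A reader might infer that physiotherapy is wholly uncontrolled. The text does not support that. It is required in both groups and limited to one or two sessions a week, which is partial control by restriction. What stays open is the frequency within that band and its stability.

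A reader might also infer that changes during the study would go entirely unnoticed. That is too strong. Controls are asked in person about their health and daily activities, and the booklet promised to both groups is to mention activities started during the period. Neither provision names physiotherapy. Recording of concomitant therapy may also be set out in a fuller protocol or analysis plan that is not shown, so the lack of detail here is not an omission in itself.

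It is also tempting to say that different sites or recruiters will enrol different populations. The article describes one city, one association's telephone list and one rehabilitation centre, so that has no documented basis.

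Finally, the Discussion's remark, "Dance replaces treatments or exercises that sometimes discourage patients", could be taken as a claim that this trial will show dance replacing physiotherapy. It is general commentary on dance. The stated objective is a comparison with a group without the intervention, and no replacement hypothesis is planned.

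The session counts are a permitted range between individuals and not a measured difference between groups. Session length and content are not given, so equal counts do not imply equal effect.

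**Conclusion.** The point holds in a limited form. The second activity exclusion, applied as written, can remove patients whom the inclusion rule requires, and the passages need to be reconciled. The first exclusion is ambiguous only.

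The permitted frequency spans 12 to 24 sessions over the study and may be distributed differently in two non-randomized groups. The stated ANOVA names no term for it, and the stated week-12 exclusion applies to one group only. Whether this produces a material bias cannot be settled from the article. The range of 0.02 to 0.20 SD rests entirely on assumed effects and assumed imbalance, and it would be zero if the mix were equal. This is a correction worth making before recruitment, not a flaw that invalidates the comparison.

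**What to change.** 1. Reconcile the passages. State explicitly whether the required physiotherapy is exempt from each of the two activity exclusions and from the week-12 rule for controls.
2. Ask about physiotherapy frequency at the existing pre and post assessments, in the same way in both groups, and report it by group. The post value is for description, since it may itself be affected by taking part.
3. Add baseline frequency (once or twice weekly, already known from screening) to the ANOVA as a covariate or between-subject factor. Let it act on the change over time, since otherwise it does not adjust the group-by-time comparison, and leave out a further interaction with group.
4. Describe the estimate as the effect of samba in patients already receiving physiotherapy.

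The cost is a few words in the criteria, one question at two contacts that already take place, one degree of freedom, and a slightly narrower description of the result.
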